#### Outcomes {12}

Primary target variables:

Patient-related outcome measures (PROMs):Oswestry Disability Index (ODI)

Secondary target variables:Health questionnaire SF-36Pain intensity using the visual analog scale (VAS)Duration of the hospital stay (in days)Postoperative complicationsDuration of opioid useOperating time (in minutes)Re-admission within 3 weeks, 1 year, 2 years, 5 years postoperativelyBlood parameters for evaluating muscle damage:Creatine kinase (CK)Glomerular filtration rateMyoglobin (Mb)Erythrocyte sedimentation rateCreatine kinase: aspartate aminotransferase quotientProcalcitonin (PCT)C-reactive protein (CRP)White blood cell count (WBC)Interleukin (IL)-6

Renal parameters (e.g., creatinine clearance, glomerular filtration rate) will be measured to assess the influence of renal function on outcome measures, as creatinine kinase levels and myoglobin levels might be influenced by renal function. The severity of pain is determined using the visual analog scale (VAS). The scale is a 10-cm-long straight line, at the ends of which the extreme points of the pain to be measured are noted (0 cm = no pain, 10 cm = worst imaginable pain). The patient is asked to mark the intensity of his pain on the line with a pen [8].

The VAS is collected on the examination days before treatments (e.g., physiotherapy) are carried out. To assess the change in pain symptoms in the patients, the VAS values of the study groups at the time of the examination are compared and compared with statistical methods. The minimal clinically relevant reduction is given for input values above 30% [8].

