#### Sample size {14}

The Institute for Medical Biometry and Statistics at the University of Freiburg, Germany, provided biometric advice. The sample size estimate of this confirmatory study (superiority study) is based on the primary target value “Oswestry Disability Index (ODI).” The ODI is the gold standard of patient-related outcome measures (PROMs) in patients after spinal surgery [9, 12].

Null hypothesis: H0: *T*-*S* = *δ*

Alternative hypothesis: Ha: *T*-*S* > *δ*

Test statistic: *Z* = (*d*-*δ*)/*sd*

*T*: full endoscopic therapy; *S*: microsurgical therapy (standard/control); *δ*: “clinically accepted limit of superiority”; *d*: true difference in the mean between the two groups; *sd*: standard error of *d*

Calculation of the sample size:$$N=2\times \frac{{\left({Z}_{1-\alpha }+{Z}_{1-\beta}\right)}^2}{\delta -{\delta}_0}\times {s}^2$$

*N* = number of cases per group; z1-α/1 − *β* = standard deviation for a one-sided 1-*α* or 1 − *β*; *δ* = true difference in the mean between the two groups; *δ*0 = clinically acceptable limit of the mean value difference (“relevance limit”); S2 = variance

With an expected difference *d* in the mean value between the two groups of *d* = 8 (maximum number of points 45 points in the ODI), an assumed standard deviation of *s* = 10, a clinically acceptable limit for the mean difference of *δ*0 = 4, a 5% level of significance (*α* = 0.05), an equivalent allocation to the groups (*k* = 1) and an assumed 10% drop-out rate, a number of cases of *n* = 87 per group, or a total of *n* = 174 is required to achieve a power of 80% (1 − *β* = 0.8).

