### Statistical methods

#### Statistical methods for primary and secondary outcomes {20a}

Descriptive statistics will be applied to the data (mean, standard deviation, median, interquartile ranges, frequencies). The Shapiro-Wilk test will be used as a normality test. Normally distributed data will be analyzed using repeated measure ANOVA and paired *t*-tests, whereas non-normally distributed data will be analyzed using the Friedman and Wilcoxon tests. We will also generate and evaluate quotients of inflammatory parameters to evaluate their impact on PROMs. An initial screening of all outcome parameters will be performed with explorative statistical approaches and univariate analyses to evaluate which combination of parameters and quotients might be relevant for PROMs. A *p* < 0.05 will be considered significant.

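### The only analyses named for relating inflammatory markers to PROMs are univariate screens with no term for surgical technique, so a marker could be flagged merely because technique shifts both it and the ODI

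*Protocol article*

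**What the plan says.** Section {20a} of the protocol article states the aim: "We will also generate and evaluate quotients of inflammatory parameters to evaluate their impact on PROMs". The method follows at once: "An initial screening of all outcome parameters will be performed with explorative statistical approaches and univariate analyses", with the purpose "to evaluate which combination of parameters and quotients might be relevant for PROMs". The paragraph closes by saying that a p-value below 0.05 "will be considered significant". The other tests in that paragraph (repeated-measures ANOVA, paired t-test, Friedman, Wilcoxon) compare values of one variable and do not relate a marker to a PROM.

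Three other places bear on the point:

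- The Background {6a} presents blood markers as surrogates for muscle damage and says the evidence on how the two techniques compare is still insufficient. It names muscle trauma as a particular focus of the comparison.
- Sample size {14} plans for a difference in the ODI: "With an expected difference *d* in the mean value between the two groups of *d* = 8", with "an assumed standard deviation of *s* = 10".
- Outcomes {12} says that renal parameters "will be measured to assess the influence of renal function on outcome measures", because creatine kinase and myoglobin may depend on renal function.

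The article does not say whether the marker screen pools the two techniques, stratifies by them, or is followed by an adjusted model.

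**The concern.** The stated question is whether a marker has an impact on a PROM. A univariate test of marker against PROM asks something else: whether the two are associated at all among the patients analysed. In pooled patients the two questions come apart when technique shifts both variables. The trial plans for a shift in the ODI and investigates a shift in the markers. Technique is then a common cause, and the pooled test tends to reject even if the marker carries no information about function within either arm.

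At stake is the reading of the exploratory results. A marker flagged in this way could be reported as evidence that less inflammation or muscle damage leads to better function, when it only reflects which operation the patient had. A correction for the number of tests would not address this, because the association in the pooled sample is real; it is the interpretation that fails.

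**Working it through.** **Inputs.** From Sample size {14}: ODI difference 8, SD 10, relevance limit 4, one-sided alpha 0.05, power 80%, 1:1 allocation, 10% drop-out, 87 per group. Assumed here, because the article gives no figure: a standardised marker difference between arms of 0.25 to 1.5 SD, normal distributions, and a two-sided 0.05 level for the marker-ODI test.

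**1. The plan's own figure.** With the effective difference squared in the denominator, n = 2 × (1.645 + 0.842)² × 10² / (8 − 4)² = 77.3, so 78 per group. Allowing for drop-out, 78 / 0.9 = 86.7, so 87. The stated 87 is reproduced, and 78 per arm (156 in total) is the number expected to be analysed.

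**2. Standardised ODI effect.** Planned: 8 / 10 = 0.8 SD. Half of that, which equals the relevance limit: 4 / 10 = 0.4 SD.

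**3. Correlation induced by pooling.** Let the arms differ by dY in the ODI and dM in the marker, in within-arm SD units, with no link within arms. With equal arms the covariance is dY·dM/4 and the variances are 1 + dY²/4 and 1 + dM²/4. Hence

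r = [dY / √(dY² + 4)] × [dM / √(dM² + 4)].

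For dY = 0.8 and dM = 0.5: r = 0.371 × 0.243 = 0.09. On Fisher's z scale the expected test statistic is about 0.0903 × √153 = 1.12. The chance of exceeding 1.96 is therefore about 20%.

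**4. Simulation.** 20,000 trials per setting, 78 per arm, marker and ODI independent within each arm. The entries are the share of trials with p < 0.05 for the pooled univariate test.

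| Marker difference (SD) | ODI effect 0.8 SD: induced r | ODI effect 0.8 SD: pooled test | ODI effect 0.4 SD: pooled test |
|---|---|---|---|
| 0.25 | 0.05 | 8.7% | 6.1% |
| 0.5 | 0.09 | 20.2% | 8.9% |
| 0.8 | 0.14 | 40.6% | 15.0% |
| 1.0 | 0.17 | 55.5% | 19.3% |
| 1.5 | 0.22 | 81.5% | 31.3% |

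With an arm term the rate is 4.7% to 5.3% in every setting. If technique affects only the marker or only the ODI, the pooled test also stays at about 5%.

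**The case against.** A reader might infer that the protocol finally judges impact by univariate tests, and that a positive trial would therefore manufacture false marker findings. The article does not support that reading, for four reasons.

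- It calls the work an initial screening and lists explorative approaches beside the univariate ones. Its purpose is to find combinations that might matter. An adjusted model could follow in the full protocol or in an analysis plan that is not shown.
- It does not say that the techniques are pooled. A univariate screen within each arm would avoid the problem entirely. Section {20b} says that no subgroup analyses are planned for now, which makes pooling the more natural reading but does not settle it.
- The size rests on a marker difference that the article does not give. The high rates need a large marker difference together with the full planned ODI effect.
- Tissue damage may lie on the path from surgery to function. A marker would then partly mediate the effect, and not all of a pooled association would be spurious. If the interest is purely prognostic, the unadjusted association is a legitimate quantity.

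Nor can one say that renal function is ignored: Outcomes {12} states an intention to examine it, although a one-predictor screen makes no use of it. The Discussion also cautions that laboratory markers are surrogates.

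All of this limits the point but does not remove it. The article states a causal-sounding aim, attaches a significance threshold and names only methods without a technique term. If a later model exists, a screen affected by treatment would still pass it the wrong candidates.

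**Conclusion.** The point holds as a mismatch between a stated aim and the only methods named for it. It is conditional on two things: that the arms are pooled, and that technique truly shifts both the marker and the ODI, as the trial's own hypotheses allow. Under those conditions, and with 78 per arm and the planned ODI effect, a marker with no within-arm relation to the ODI would be flagged in about 9% to 82% of trials across the assumed marker differences. Where both effects are small (0.4 SD for the ODI, 0.25 to 0.5 SD for the marker) the rate is about 6% to 9%, only a little above nominal. The figures apply to the randomised patients alone. Pooling in the preference cohort would raise the sample size, and with it the rejection rate for a given induced correlation.

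The aim is exploratory, and neither the primary 1-year ODI comparison nor its sample size is affected. The change is worth making because it is cheap, not because the trial's main conclusion is at risk.

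**What to change.** In section {20a}, state that each model relating a marker or quotient to a PROM includes surgical technique, the baseline PROM and the preoperative marker value. If randomised and preference patients are analysed together, add a term for cohort. For creatine kinase and myoglobin, add the GFR. The technique term is what restores the 5% rate; the other terms account for differences present before surgery and for the renal influence that the article itself names. Report the coefficient as an association within arms, and drop the word impact.

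No new data are needed. Preoperative blood samples are planned in {11a}, preoperative PROMs in {7} and {12}, and GFR in {12}. The cost is a few degrees of freedom. The adjusted coefficient also does not capture any part of the surgical effect that runs through the marker. If mediation is of interest, it should be posed as a separate question.

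### The sample size assumes a one-sided test against a 4-point limit, but the statistical methods section does not carry that test into the primary analysis

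*Protocol article*

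**What the plan says.** Sample size {14} calls the study confirmatory and sets out a complete test:

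- The alternative is shifted by a limit: "Alternative hypothesis: Ha: *T*-*S* > *δ".
- The statistic is measured from that limit: "Test statistic: *Z* = (*d*-*δ*)/*sd".
- The quantiles in the formula are one-sided: "standard deviation for a one-sided 1-*α".
- The inputs include "With an expected difference *d* in the mean value between the two groups of *d* = 8" and "a clinically acceptable limit for the mean difference of *δ*0 = 4, a 5% level of significance (*α* = 0.05", together with SD 10, equal allocation, 10% drop-out and 80% power. The result is 87 per group, 174 in total.

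The notation shifts within the section. The hypotheses use δ for the limit, while the formula uses δ for the true difference and δ0 for the limit. The limit is 4 in either case.

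Outcomes {12} makes 1-year ODI the main time point.

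Statistical methods for primary and secondary outcomes {20a} names repeated-measures ANOVA and paired t-tests for normal data, and Friedman and Wilcoxon tests otherwise. It then describes exploratory screening and ends with "A *p* < 0.05 will be considered significant". It mentions no limit, shifted null or side. No other section applies the limit to the analysis.

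**The concern.** The sample size section sets a demanding bar: the endoscopic benefit must be shown to exceed 4 points, not merely to exceed zero. An analyst who opens only the section on methods for the primary outcome will not find that bar. None of the tests named there is conventionally run against a shifted null, and the omnibus ones (repeated-measures ANOVA, Friedman) cannot test a one-sided hypothesis of a difference above 4.

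Two analysts could therefore each follow a section of the same document and reach opposite conclusions on the same data. The claim at stake is the trial's main one, superiority over the gold standard. It could be made on a difference smaller than the protocol's own relevance limit.

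**Working it through.** **Inputs.** All are from Sample size {14}: expected difference 8, limit 4, SD 10, α = 0.05 one-sided, power 80%, allocation 1:1, drop-out 10%.

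**1. Reproduce the stated sample size.**

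n = 2 × (1.645 + 0.8416)² × 10² / (8 − 4)² = 77.3, so 78 evaluable per group. Then 78 / 0.9 = 86.7, so 87 per group and 174 in total. This matches exactly.

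The calculation squares the denominator. The formula as printed does not, and would give about 309 per group before drop-out. The stated figure therefore comes from the squared form.

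**2. Try the other readings.**

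| Test | Evaluable per group | With 10% drop-out |
|---|---|---|
| One-sided 5%, against 4 | 78 | 87 |
| Two-sided 5%, against 4 | 99 | 110 |
| One-sided 5%, against 0 | 20 | 23 |
| Two-sided 5%, against 0 | 25 | 28 |

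Of these four, only the one-sided test against the limit gives 87.

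**3. Observed difference needed for significance.** Section {20a} does not clearly name a two-sample comparison, so I assume one: difference in means, normal approximation, 78 evaluable per group, SD 10.

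Standard error = 10 × √(2/78) = 1.601.

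- Against zero, one-sided: 1.645 × 1.601 = 2.63 points.
- Against zero, two-sided: 1.96 × 1.601 = 3.14 points.
- Against 4, one-sided (the sized test): 4 + 1.645 × 1.601 = 6.63 points.

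Both thresholds against zero lie below the limit of 4. With all 87 per group evaluable they are 2.49 and 2.97.

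**4. Probability of declaring superiority.** At a true difference of 4, the null boundary in {14}, 4 / 1.601 = 2.498. The one-sided probability is Φ(2.498 − 1.645) = 0.803, and the two-sided probability is Φ(2.498 − 1.96) = 0.705. The other rows follow in the same way.

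| True difference | Zero null, one-sided | Zero null, two-sided | Sized test |
|---|---|---|---|
| 2 | 34.6% | 23.9% | 0.2% |
| 3 | 59.0% | 46.5% | 1.2% |
| 4 | 80.3% | 70.5% | 5.0% |
| 8 | 99.96% | 99.9% | 80.3% |

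**5. Two-sided against the limit.** The observed difference would have to exceed 4 + 1.96 × 1.601 = 7.14 points. Power at a true difference of 8 would be 70.5%, and 80% would need 99 evaluable (110 enrolled) per group, 220 in total.

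**The case against.** The best defence is that the primary test is already specified. Sample size {14} gives hypotheses, a test statistic, a side and α, and a test statistic is an analysis specification as well as a planning input. The closing sentence of {20a} uses the same 5%, covers all outcomes and can be read as the threshold for that test. Nothing in {20a} says that the null is zero or that superiority will be claimed on the generic threshold.

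This stands in part: the shifted test is in the document, so it has not been abandoned. A reader might infer that the plan has adopted a test against zero as its success rule, but the text does not establish that. What remains is that the section on primary-outcome methods names specific tests, none of which is by convention the test in {14}, and does not refer back to it. That is more than detail left to a fuller document.

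Three further objections stand:

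- The thresholds and probabilities assume a two-sample comparison of means. Paired t-tests and the Friedman test are within-patient methods, and Outcomes {12} says no repeated-measures comparison is planned. That is a separate problem, but it makes the figures conditional.
- The 80% and 70% are error rates only against the null in {14}. At a true benefit of 4, rejecting zero is correct in itself.
- A reader might infer that the trial falls short of 80% power because p-values are usually two-sided. The document nowhere mentions two-sided testing, so the 70% figure is only a contingency.

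**Conclusion.** The concern holds as a mismatch between two sections. Sample size {14} fixes a one-sided 5% test against 4 points, and the sample size is correct for that test. Section {20a} does not carry it forward.

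If {20a} is applied as a between-group test against zero, the observed difference needed falls from about 6.6 points to about 2.6 (one-sided) or 3.1 (two-sided). Any result between the lower figure and 6.6 would be a success under one section and a failure under the other. At a true difference of 4, the chance of declaring superiority is about 80% or 70% instead of 5%. These sizes rest on 78 evaluable per arm, SD 10 and a two-sample comparison of means. The mismatch itself does not depend on those assumptions.

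**What to change.** State in {20a} that the primary analysis is the test defined in {14}: a between-group comparison of 1-year ODI, with superiority claimed only if the lower one-sided 95% confidence bound of the benefit exceeds 4. Report the test against zero as secondary. Three details must be settled for the rule to work:

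- **Direction.** Lower ODI is better, so define the benefit as microsurgical minus endoscopic and correct the sign of T−S in {14}. As written, on raw scores, it points toward worse endoscopic results.
- **Scale.** Outcomes {12} scores the ODI as a percentage, whereas {14} refers to a maximum of 45 points. Four points of 45 would be 4/45 = 8.9 percentage points. State the scale used for sizing and apply the limit of 4 on it.
- **Non-normal data.** The rule concerns a mean difference, which a Wilcoxon test does not provide. Say how the rule applies if that branch is taken.

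The cost is a few sentences in {20a} and matching corrections in {14}, with no additional patients. The 87 per group and 80% power stand. Only if the sponsor intends p < 0.05 as two-sided against the limit must power be restated as about 70%, or the sample size raised to 110 per group.

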#### Interim analyses {21b}

Interim results will be analyzed at 1 year, 2 years, and 5 years to allow constant evaluation of the surgical outcome for patients. Interim results will be communicated to all research study members. Cancelation of the trial or the decision to publish preliminary results of high relevance to the research community will be decided after an in-depth discussion and consensus with all research study members and the responsible institutional review board.

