The Oswestry Disability Index (ODI) is a questionnaire for evaluating functional disorders caused by back pain. The German version published in 2006 [9], the ODQ-D (Oswestry Disability Questionnaire- German), is scientifically recognized, and researchers regularly use it in back pain studies. The questionnaire is divided into 10 sections, each with 6 possible answers with point values of 0–5 points. The most appropriate answer should be ticked. As a result, the number of points achieved is set in relation to the maximum number of points and given as a percentage. Based on the results, the following judgments are made: 0–20% equals minimal, 21–40% equals moderate, 41–60% equals severe, 61–80% equals crippled, and 81–100% equals bed-bound or patients exaggerating their symptoms. The ODI will be measured as the primary outcome. The following time points will be assessed for the ODI: preoperatively, immediately postoperatively, 24 h, 48 h, 3 weeks, 1 year, 2 years, 3 years, and 5 years postoperatively (see also participant timeline {13}). The main outcome time point will be the 1-year evaluation. There is no repeated measure design statistical comparison planned and the 1-year, 2-year, 3-year, and 5-year outcome will be evaluated separately to evaluate the effectiveness of the respective treatment constantly for patients.

The SF-36 (Short Form Health 36) consists of 36 questions and is a general health questionnaire that uses 8 different dimensions to make statements about the patient’s state of health. It includes statements about the following: vitality, physical functioning, bodily pain, general health perceptions, the physical role of functioning, social role of functioning, and mental health.

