### Assignment of interventions: blinding

#### Who will be blinded {17a}

The researchers analyzing the final data will be blinded.

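### The analyses called interim at 1, 2 and 5 years have no stated clock, can lead to cancellation or early publication, and go to the whole team, including those who enrol, obtain consent, operate and collect outcomes

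*Protocol article*

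**What the plan says.** All references are to the Protocol article.

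- **Timing.** Section {21b} plans the looks as follows: "Interim results will be analyzed at 1 year, 2 years, and 5 years to allow constant evaluation of the surgical outcome for patients". The starting point of these years and the data cut for each look are not given.
- **Recipients.** The same section: "Interim results will be communicated to all research study members".
- **Consequence.** The same section allows the results to lead to stopping the trial or to early publication. The decision is by consensus of the members together with the institutional review board.
- **Primary time point.** Outcomes {12}: "The main outcome time point will be the 1-year evaluation". The later years are to be evaluated separately.
- **Threshold.** Statistical methods {20a}: "A *p* < 0.05 will be considered significant". Sample size {14}, which calls the study confirmatory, uses "a 5% level of significance" with a one-sided quantile ("standard deviation for a one-sided").
- **Blinding.** Section {17a}, on who is blinded: "The researchers analyzing the final data will be blinded". Section {17b} confirms that surgeons and patients are not blinded.
- **Oversight.** Section {21a} says that there is no external data monitoring committee. Section {5d} lists four research members.
- **Calendar.** Trial status: recruitment began on 14 January 2022 and is planned to finish by 30 December 2025.

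**The concern.** An interim look that can end a trial or put its results in print needs three things fixed: when it happens, on which data, and who sees it. Here the first two are open, and the third is settled in the least protective way, because nobody is exempt.

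This matters more than usual in this design. One surgeon operates and also screens and enrols. Patients may decline randomisation and enter the parallel non-randomised arm, so the consent conversation shapes who is randomised. The primary outcome is self-reported by patients who know their operation. If comparative results circulate while patients are still being recruited and followed, they could colour how the techniques are explained, who is enrolled and how patients rate themselves. A second issue, which depends on the reading, is error control: repeated claims at an unadjusted 5% would exceed the nominal level.

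**Working it through.** **1. The plan's own sample size.** Inputs from Sample size {14}: expected difference 8, relevance limit 4, SD 10, one-sided alpha 0.05, power 80%, drop-out 10%. With the net difference squared in the denominator:

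n = 2 × (1.645 + 0.842)² × 10² / (8 − 4)² = 77.3, so 78 per group; 78 / 0.9 = 86.7, so 87 per group and 174 in total.

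This matches the stated figure. It is a fixed design with one analysis, so it contains no allowance for repeated looks.

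**2. Who receives the results.** Matching the roles across sections, the four members in {5d} are:
- the surgeon, who also screens and enrols ({11c}, {16c});
- the member who assigns participants ({16c}), who together with the surgeon obtains consent ({26a});
- two members who obtain the questionnaires ({18a}), manage the data ({19}) and assess outcomes ({21a}).

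Every listed member therefore has a role in consent, enrolment, assignment, surgery or outcome collection.

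**3. Calendar reading.** Recruitment spans 14 January 2022 to 30 December 2025, which is 1,446 days. Assuming uniform accrual:

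| Look | Recruited | 1-year ODI due |
|---|---|---|
| Year 1 | 365/1446 = 25% | 0% |
| Year 2 | 730/1446 = 50% | 365/1446 = 25% |
| Year 5 | 100% | 100% |

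The first two looks fall within recruitment, and at year 2 about half of the patients are still to be enrolled. For the primary endpoint there is effectively one early look (25% of the information) and one final look. The correlation of the two test statistics is √(0.25/1) = 0.5. If efficacy were claimed at p < 0.05 at either look:

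- one-sided: 1 − P(Z₁ ≤ 1.645, Z₂ ≤ 1.645) = 8.8%;
- two-sided: 1 − P(|Z₁| ≤ 1.96, |Z₂| ≤ 1.96) = 9.1%.

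**4. Follow-up reading.** If each look waits until all patients have reached that visit, the 1-year look is the primary analysis. It is run once on complete data, and its error is 5%. The 2- and 5-year looks test other time points. Only if the three were treated as equal claims does the chance of at least one false positive rise. For three equally correlated normal statistics (the correlation is an assumption):

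| Correlation | One-sided | Two-sided |
|---|---|---|
| 0.5 | 11.8% | 12.5% |
| 0.7 | 10.3% | 10.9% |

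**The case against.** The follow-up reading has real support. Objectives {7} lists 1, 2 and 5 years among the assessment times, and Outcomes {12} justifies the separate yearly evaluations in terms much like those of {21b}. It also names 1 year as the main time point. On that reading no error rate for the primary test is inflated. This stands, and it is why the error figures are given only conditionally.

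Four stronger inferences are tempting, and the documents do not support them:

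- **That p < 0.05 is a stopping rule.** The threshold sits in a general statement in {20a}. Section {21b} ties no p-value to any action and does not say that cancellation would be for efficacy; stopping for harm or futility would not raise the superiority error. Boundaries may also be in an analysis plan that is not at hand.
- **That there are three full looks at the primary endpoint.** Under the calendar reading year 1 has essentially no 1-year ODI, so the error rate for three equally spaced looks fits neither reading.
- **That the analyst blinding is undone.** Section {17a} does not say who the analysts are, and {21b} does not say that results are shown by identified arm. Both are plausible, since evaluation is in-house and nobody is excluded, but they are inferences.
- **That bias is certain.** Surgeon and patients are unblinded anyway, and allocation uses sealed opaque envelopes. The added effect of interim knowledge cannot be quantified. A shift in who accepts randomisation would bear mainly on accrual and generalisability.

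What the objection does not remove is that {21b} affirmatively sends the results to everyone and makes the same people party to the decision. An analysis plan could add a boundary, but it could not restrict access without contradicting that section.

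**Conclusion.** The point holds as a defect in what {21b} fixes: the clock and data cut are undefined, the looks may lead to cancellation or early publication, and the results go to all members, each of whom has a role in enrolment, consent, surgery, assignment or outcome collection.

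Its size depends on the reading. In calendar time, two looks fall within recruitment and comparative results could influence the trial's conduct. If efficacy were also claimed at p < 0.05 at each look, type I error would be about 9% (8.8% one-sided, 9.1% two-sided) under uniform accrual. In follow-up time on complete data, the primary test keeps its 5%, the label interim is wrong, and the 10-13% applies only to an unranked set of 1-, 2- and 5-year claims with correlation 0.5-0.7. A reader might conclude that the type I error exceeds 5% in any case; that does not follow. The section needs correcting on either reading.

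**What to change.** Reword {21b} to state that:

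1. the one confirmatory ODI comparison is run once, after the last randomised patient's 1-year visit;
2. no between-arm efficacy result is produced or circulated before then;
3. the 2- and 5-year comparisons are secondary and are not called interim;
4. any earlier review is limited to complications and trial conduct.

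The cost is protocol wording, communicated to the review board and the registry as {25} provides. The downside is that the team gives up an early efficacy look during recruitment. If the sponsor wants to keep such a look, it would need a stated data cut, a prespecified allocation of the 5%, and someone outside the four listed members to see the comparative results. That is more than a change of wording.
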